| **Population: Inclusion of special groups (Check all that apply):**   | Gender  X Male  X Female  Age  X 0 – 4 years  5 – 9 years  10 – 19 years  X 20 – 64 years  65 + | Pregnant Women  Fetuses  Prisoners  Destitutes  Service Providers  Cognitively Impaired  CSW  Others (specify      )  Animal | | --- | --- |   NOTE It is the policy of the Centre to include men, women, and children in all research projects involving human subjects unless a clear and compelling rationale and justification (e.g. gender specific or inappropriate with respect to the purpose of the research) is there. Justification should be provided in the `Sample Size’ section of the protocol in case inclusiveness of study participants is not proposed in the study. | | | | | | |
| **Project/study Site (Check all the apply):**  Dhaka Hospital  Matlab Hospital  Matlab DSS Area  Matlab non-DSS Area  Mirzapur  Dhaka Community  Chakaria  Abhoynagar | | Mirsarai  Patyia  X Other areas in Bangladesh  Outside Bangladesh  Name of Country:  Multi Centre Trial  (Name other countries involved): | | | | |
| Type of Study (Check all that apply):   | Case Control Study  X Community-based Trial/Intervention  Program Project (Umbrella)  Secondary Data Analysis  Clinical Trial (Hospital/Clinic)  Family Follow-up Study | Cross Sectional Survey  Longitudinal Study (cohort or follow-up)  Record Review  Prophylactic Trial  Surveillance/Monitoring  X Others: Controlled before-after study | | --- | --- |   NOTE: Does the study meet the definition of clinical studies/trials given by the International Committee of Medical Journal Editors (ICMJE)? Yes  No    Please note that the ICMJE defined clinical trial as “*Any research project that prospectively assigns human subjects to intervention and comparison groups to study the cause-and-effect relationship between a medical intervention and a health outcome*”.    If YES, after approval of the ERC, the PI should complete and send the relevant form to provide required information about the research protocol to the Committee Coordination Secretariat for registration of the study into websites, preferably at the [www.clinicaltrials.gov](http://www.clinicaltrials.gov/). It may please be noted that the PI would require to provide subsequent updates of the research protocol for updating protocol information in the website. | | | | | | |
| **Targeted Population (Check all that apply):**  No ethnic selection (Bangladeshi)  Bangalee  Tribal group | | Expatriates  Immigrants  Refugee | | | | |
| **Consent Process (Check all that apply):**  Written  Oral  None | | X Bengali Language  English Language | | | | |
| **Proposed Sample Size:** 1160 in baseline and end line will be interviewed  Sub-group (Name of subgroup (e.g. Men, Women) and Number   | Name | Number | Name | Number | | --- | --- | --- | --- | | (1) households | 1160 | (3) NGO providers | 8 | | (2) private sector providers | 20 |  |  |   Total sample size: 1188 | | | | | | |
| **Determination of Risk: Does the Research Involve (**Check all that apply**):**   | Human exposure to radioactive agents?  Fetal tissue or abortus?  Investigational new device?  (specify:      )  Existing data available from Co-investigator | Human exposure to infectious agents?  Investigational new drug  Existing data available via public archives/sources  Pathological or diagnostic clinical specimen only  Observation of public behaviour  New treatment regime | | --- | --- | | | | | | | |
| **Could the information recorded about the individual if it became known outside of the research:**   | Yes  X | No | Is the information recorded in such a manner that study participants can be identified from information provided directly or through identifiers linked to the study participants? | | --- | --- | --- | | Yes | No  X | Does the research deal with sensitive aspects of the study participants’ behaviour; sexual behaviour, alcohol use or illegal conduct such as drug use? |  | Yes | No  X | Place the study participants at risk of criminal or civil liability? | | --- | --- | --- | | Yes | No  X | Damage the study participants’ financial standing, reputation or employability, social rejection, lead to stigma, divorce etc.? | | | | | | | |
| **Do you consider this research (Check one):**  Greater than minimal risk X No more than minimal risk  Only part of the diagnostic test  Minimal Risk is "a risk where the probability and magnitude of harm or discomfort anticipated in the proposed research are not greater in and of themselves than those ordinarily encountered in daily life or during the performance of routine physical, psychological examinations or tests. For example, risk of drawing a small amount of blood from a healthy individual for research purposes is no greater than the risk of doing so as a part of routine physical examination". | | | | | | |

| Alternative, sustainable interventions in support of zinc treatment for childhood diarrhea need to be identified. Within the NGO sector, direct provision of health services is provided, however some NGOs also work closely with the private sector providers. Hypothetically, this avoids unnecessary duplication of effort and enhances the quality of the care provided in the private sector. This study will provide objective evidence of the impact of this approach, using the scale-up of zinc for the treatment of childhood diarrhoea as a test case. The study will be assessing NGO impact among unregulated (unlicensed), rural service providers. Further, this study will serve to assess the value of this model of scaling up activities in the non-state sector with a particular eye toward more generalizable and replicable improvement in quality of care strategies between NGOs and unlicensed private providers. This will be controlled before-after (CBA) study. An equivalent control area will be included in the study. The objective is to document changes in zinc and antibiotic as well as anti-diarrhoeal usage in childhood diarrhea following a scale-up intervention package delivered by a local NGO to local private providers. This will include sensitization, training and follow-up support. Impact will be assessed in terms of changes in zinc coverage and antibiotic use among households in the catchment population served by these providers. The study will be conducted in four unions located in Sreepur Upazila within Gazipur district, located north to Dhaka. Two of the unions, namely Rajabari and Prohladpur comprising 55 villages with 15,530 households and an estimated 76,150 population will serve as intervention area. The other two unions Telihat and Barmi will be taken as control sites. They contain 53 villages with 19,898 households and an estimated 99,000 population. The curative health services in these sites are provided by local drug vendors, village practitioners, traditional healers, and licensed government, private or NGO health service providers. Data will be collected through survey and in-depth interviews. Data will be entered and analyzed using SPSS version 12.0. Absolute counts, proportions, and means with 95% confidence interval will be calculated. These and regression analysis will be done using STATA version 9, cluster survey program, that accounts for potential within cluster homogeneity. Based upon the household surveys, the outcomes that will be calculated are: coverage-the proportion receiving zinc, ORS (zinc and ORS), and antibiotics or antidiarrhoeals and changes in coverage 6 months following the introduction of the intervention package, equity: who is receiving zinc by age, gender and socioeconomic status. For differences in categorical outcomes crude relative risks and 95% confidence intervals will be determined. It is expected that the study will help in increasing zinc coverage for the treatment of children under five years of age and decrease in the use of antibiotics and antidiarrhoeals within the NGO catchment population. |

# Description of the Research Project

## Hypothesis to be Tested:

Concisely list in order, the hypothesis to be tested and the Specific Aims of the proposed study. Provide the scientific basis of the hypothesis, critically examining the observations leading to the formulation of the hypothesis.

That an NGO initiated sensitization, training and support package to scale up the prescribing of

zinc among NGO and private sector providers for the treatment of acute childhood diarrhea will,

within 4 months, result in:

H1. A significant increase in zinc coverage for the treatment of children under five years of age

within the NGO catchment population, and

H2. A significant decrease in the use of antibiotics and antidiarrhoeals

## Specific Aims:

Describe the specific aims of the proposed study. State the specific parameters, biological functions/ rates/ processes that will be assessed by specific methods.

# General objectives

To assess the impact of an NGO zinc scale up package developed to maximize compliance with WHO/UNICEF and MOHFW zinc treatment recommendations for acute childhood diarrhea (ACD)

# Specific Research objectives

Following the implementation of the proposed scale-up intervention package by a local NGO, Dushtha Shasthya Kendra (DSK).

- - to document changes in zinc coverage for ACD
  - to document changes in inappropriate use of antibiotics and antidiarrheals
  - to identify barriers/disincentives to the prescribing of zinc treatment among private providers.

## Background of the Project including Preliminary Observations

Describe the relevant background of the proposed study. Discuss the previous related works on the subject by citing specific references. Describe logically how the present hypothesis is supported by the relevant background observations including any preliminary results that may be available. Critically analyze available knowledge in the field of the proposed study and discuss the questions and gaps in the knowledge that need to be fulfilled to achieve the proposed goals. Provide scientific validity of the hypothesis on the basis of background information. If there is no sufficient information on the subject, indicate the need to develop new knowledge. Also include the significance and rationale of the proposed work by specifically discussing how these accomplishments will bring benefit to human health in relation to biomedical, social, and environmental perspectives.

Diarrhoeal disease is the second leading cause of under-five mortality in developing countries, accounting for 1.5 to 2 million deaths per year (1,2). The large majority of these deaths can be prevented by the timely use of oral rehydration solutions (ORS), zinc treatment and continued feeding practices (3).

## Zinc as a treatment for childhood diarrhoea:

Several randomized hospital and community-based trials have consistently demonstrated the efficacy of zinc treatment for acute or persistent diarrhoea in children under-five years of age (4,5,6,7,8,9).

Pooled or meta-analyses of published studies demonstrate that zinc supplementation reduces the duration and severity of acute diarrhoea and reduces the likelihood of a prolonged episode (10,11). It is estimated that the incidence and prevalence of childhood diarrhoea can be reduced by 18% (95% CI, 7-28%) and 28% (95% CI, 12-37%) respectively in zinc treated children (10). A community-based, effectiveness trial of zinc treatment for acute childhood diarrhea was carried out in the ICDDR,B rural field site located in Matlab. In this trial, in which children received daily zinc treatments with each episode of diarrhoea, the children in the zinc intervention group had a shorter duration of illness, a reduced likelihood of a repeat diarrhoea episode and reduced non-injury mortality. The reduction of mortality was substantial, being 50% (12).

WHO has estimated the global annual mortality burden attributable to zinc deficiency to be 750,000 deaths per year (13). It is anticipated that over one-half of these deaths could be averted through the successful application of zinc as a treatment for childhood diarrhea (14).

**WHO/UNICEF joint statement on diarrhoea management:**

Given this potential mortality reduction and the strength of the evidence at hand in support of zinc treatment, WHO/UNICEF issued a joint statement on updated guidelines for the management of childhood diarrhea in May, 2004(15). This includes the recommendation that all children under five be treated with zinc (20 mg/day if 6-59 months and 10 mg/day if less than 6 months of age) for 10 to 14 days. This recommendation is now a policy of the Ministry of Health and Family Welfare, with the slight modification to include children starting at two months of age.

The WHO/UNICEF joint statement calls for countries to assess progress in controlling diarrhoeal diseases, prioritize the availability of ORS and zinc supplements, strategize educating health workers at all levels about the use of zinc, and promote the availability of zinc further research into scaling up the use of zinc.

# Scaling up of Zinc:

Zinc scaling up efforts in Bangladesh focus on collaboration among ICDDR,B, the Ministry of Health and Family Welfare, ACME Laboratories and many other public and private sector organizations. The aim of this collaboration is to provide zinc treatment for diarrhoea on a national scale, targeting the entire under-five year-old population of Bangladesh. It has been estimated that zinc treatment could save the lives of up to 50,000 children per year in Bangladesh alone (12).

At present, the SUZY project has adopted the following scale-up strategies:

1. A mass media campaign
2. Provider promotion through ACME sales representatives
3. Orientation sessions with licensed providers
4. Training workshops for village doctors
5. Integration of zinc treatment into IMCI protocols (public sector)

The primary emphasis has been on reaching private providers through existing private sector channels. Thus far, we have not worked closely with the NGO sector. This could be an important,

additional strategy to further increasing zinc coverage across Bangladesh, in particular in communities highly reliant upon NGO services.

**Reduction of antibiotic usage for diarrhea:**

Antimicrobial and antidiarrhoeal drugs are unnecessary and potentially hazardous in the treatment of childhood diarrhoea. Numerous studies conducted around the globe have demonstrated that the use of zinc combined with ORS can reduce the inappropriate use of antibiotics. Baqui and colleagues found a statistically significant reduction in antibiotic use and the attitude for the treatment of childhood diarrhoea when zinc was introduced during a controlled, community-based study in Bangladesh (16). In India Bhandari et al. found a 34% reduction in the inappropriate use of tablets and a 64% reduction in the use of injections for the treatment of diarrhea after zinc was introduced (17).

**Rationale:**

In order to reach all children with diarrhoea, zinc treatment will need to be introduced and sustained within public, NGO and private service delivery systems. To improve zinc coverage, the Ministry of Health and Family Welfare (MOHFW) has initiated a program within the public sector that aims to distribute zinc, free of charge as a treatment of childhood diarrhea. However, a large population of the country, mostly the poor are served by NGO health services. Plan International, Bangladesh has been working for many years with children and families in some of the poorest communities, with aim of improving the quality of their lives, including their health. Across Bangladesh Plan works with 30 partner NGOs who provide community based services. These NGOs are highly respected within the communities they work, both among the general population and health providers. Whether these NGOs can significantly impact the diarrhoea treatment practices of private providers is unclear and should not be assumed. Past work carried out by the SUZY team with NSDP service providers plus local community sensitization and zinc promotion was not successful in improving zinc treatment coverage. The Plan model of having NGOs work with local providers is an alternative that deserves attention and validation of impact.

In Bangladesh, health seeking for childhood diarrhoea is dominated by utilization of private sector providers (18). Unlicensed providers (village doctors, drug sellers, and homeopaths) comprise more than 90% of the preferred source of care when help is sought.

The proposed study will be carried out in a rural community, where Dushtho Sasthya Kendra (DSK) [intervention area] and Ganosasthyo Kendra (GK) [control area], two partner NGOs of Plan International provide primary health care services along with other programs in Gazipur district, located north of Dhaka.

The proposed study will assess the impact of a zinc scale up intervention package that entails strong and sustained NGO-private sector collaboration. The aim is to build upon the existing mass media and provider promotion campaigns already implemented in Bangladesh, in the hope that this additional collaboration will maximize zinc treatment coverage for acute childhood diarrhoea (ACD). The impact of the zinc scale up package on inappropriate prescription/sale of antibiotics will also be assessed. The proposed study will assess the impact of a zinc scale up intervention package that entails strong and sustained NGO-private sector collaboration. We will determine whether the effort and expense of scaling up specifically with NGOs provides value added to the nation-wide programs described above as well as other changes to the public health system.

**Contribution to the Literature**

This impact study will contribute to the body of zinc/ORS and scaling up literature by employing an existing network of NGO providers in the training of unlicensed providers, not only on the use of zinc and ORS but also on the overall appropriate management of childhood diarrhea according to WHO/UNICEF standards.

**Research Design and Methods**

Describe in detail the methods and procedures that will be used to accomplish the objectives and specific aims of the project. Discuss the alternative methods that are available and justify the use of the method proposed in the study. Justify the scientific validity of the methodological approach (biomedical, social, or environmental) as an investigation tool to achieve the specific aims. Discuss the limitations and difficulties of the proposed procedures and sufficiently justify the use of them. Discuss the ethical issues related to biomedical and social research for employing special procedures, such as invasive procedures in sick children, use of isotopes or any other hazardous materials, or social questionnaires relating to individual privacy. Point out safety procedures to be observed for protection of individuals during any situations or materials that may be injurious to human health. The methodology section should be sufficiently descriptive to allow the reviewers to make valid and unambiguous assessment of the project.

**Study Design:** This will be controlled before-after (CBA) study. An equivalent control area will be included in the study. The objective is to document changes in zinc and antibiotic as well as anti-diarrhoeal usage in childhood diarrhoea following a scale-up intervention package delivered by a local NGO to local private providers. This will include sensitization, training and follow-up support. Impact will be assessed in terms of changes in zinc coverage and antibiotic use among households in the catchment population served by these providers.

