## Study sites: The study will be conducted in four unions located in Sreepur Upazila within Gazipur district, located north to Dhaka. Two of the unions, namely Rajabari and Prohladpur comprising 55 villages with 15,530 households and an estimated 76,150 population will serve as intervention area. The other two unions Telihat and Barmi will be taken as control sites. They contain 53 villages with 19,898 households and an estimated 99,000 population. Local drug vendors, village practitioners, traditional healers, and licensed government, private or NGO health service providers provide the curative health services in these sites.

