## Data Analysis

Describe plans for data analysis. Indicate whether data will be analyzed by the investigators themselves or by other professionals. Specify what statistical software packages will be used and if the study is blinded, when the code will be opened. For clinical trials, indicate if interim data analysis will be required to monitor further progress of the study.

The investigative team will carry out the data analysis. Data entry and general management will be done by Data Resources and Surveillance Unit of the Division. Data will be entered and analyzed using SPSS version 12.0. Absolute counts, proportions, and means with 95% confidence interval will be calculated. These and regression analysis will be done using STATA version 9, cluster survey program, that accounts for potential within cluster homogeneity.

Based upon the household surveys, the following outcomes will be calculated:

- Coverage: the proportion receiving zinc, ORS (zinc and ORS), and antibiotics or antidiarrhoeals and changes in coverage 6 months following the introduction of the intervention package.
- Equity: who is receiving zinc by age, gender and socioeconomic status
- For differences in categorical outcomes crude relative risks and 95% confidence intervals will be determined.

The provider interviews will be recorded and transcripts prepared. Qualitative responses will be sub-grouped by topic and response.

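### The planned village-clustered confidence intervals reflect sampling within four non-randomised unions, not differences in trend between unions or NGO areas, and the impact claim should be limited to match

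*Protocol*

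**What the plan says.** - **Design.** Research Design and Methods says "This will be controlled before-after (CBA) study" and adds that "An equivalent control area will be included in the study". The Project Summary repeats both statements.
- **Allocation.** The Rationale places the study in a rural community "where Dushtho Sasthya Kendra (DSK) [intervention area] and Ganosasthyo Kendra (GK) [control area], two partner NGOs of Plan International". Under Study sites, two DSK unions "comprising 55 villages with 15,530 households and an estimated 76,150 population will serve as intervention area", and "The other two unions Telihat and Barmi will be taken as control sites". No random allocation and no criteria for selecting the control area are given.
- **Precision.** Sample size estimation for Survey takes 580 children per group, as 29 villages of 20 children, with a design effect of 1.5. Measurement/Data collection tools defines clusters as villages. Data Analysis plans a Stata "cluster survey program, that accounts for potential within cluster homogeneity".
- **Effect measure.** Data Analysis lists changes in coverage at six months, and crude relative risks with 95% confidence intervals for categorical outcomes. Regression is mentioned without a stated contrast.
- **Use of the result.** The Project Summary says the study will give objective evidence about impact, with an eye to "generalizable and replicable improvement in quality of care strategies between NGOs and unlicensed private providers". The Rationale says it will determine whether NGO scale-up adds value to the national programmes.

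**The concern.** The intervention varies only between NGO areas, and within each area it covers both unions. No village was assigned to anything on its own. An interval that corrects for similarity among children in the same village answers a narrow question: how well the sample represents these four unions. It makes no allowance for two unions, or two NGO areas, changing differently over the same months for reasons unrelated to the package.

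Such reasons are plausible here. The sections on scaling up zinc and on the rationale describe several activities running at the same time: mass media, sales-representative promotion, workshops for village doctors and free public-sector zinc. If any of these reached one area more than the other, the difference would be credited to DSK's training. The decision at stake is whether working through NGOs adds value, and that goes beyond these four unions.

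The effect measure adds to the problem. A crude relative risk compares either before with after or one area with the other. Neither, by itself, uses the control area to remove the common trend, which is the purpose of a controlled before-after design.

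**Working it through.** **1. The plan's own figure.** Inputs from Sample size estimation for Survey: z values 1.64 and 1.28, p = 0.15, d = 0.075, C = 1.5.

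n = (1.64 + 1.28)² × 0.1275 × 2 × 1.5 / 0.075² = 579.8, so 580 per group is reproduced, and 29 × 20 = 580.

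**2. What the design effect covers.** With 20 children per village, C = 1.5 implies a village intraclass correlation of 0.5/19 = 0.026. There is no term for union or NGO area.

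**3. Village-based standard error of the difference in changes.** This takes 580 children per area in each of two independent surveys, with the plan's variance and design effect and no true effect:

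SE = √(4 × 0.1275 × 1.5 / 580) = 0.0363, or a 95% half-width of 1.96 × 0.0363 = 0.071.

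**4. Adding union-level variation in change.** Let s be the SD of union-level changes. Two unions per arm add s²(1/2 + 1/2) = s² to the variance. The protocol gives no value for s, so the range is assumed. The true one-sided error is 1 − Φ(1.645 × 0.0363 / total SE).

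| Assumed s (points) | Total SE | True error, nominal one-sided 5% | True error, nominal two-sided 5% |
|---|---|---|---|
| 0 | 0.0363 | 5% | 5% |
| 2 | 0.0415 | 7.5% | 8.6% |
| 3 | 0.0471 | 10% | 13% |
| 5 | 0.0618 | 17% | 25% |

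This treats unions as varying independently. A shift common to both unions of one NGO would not be halved by averaging and is not in the table.

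**5. Could unions serve as the units?** Four unions leave 2 degrees of freedom, with t = 4.30 against 1.96. Even with s = 0 the half-width rises from 0.071 to 0.156, which is 2.2 times wider. With NGO area as the unit, 1 against 1, no degrees of freedom remain.

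**6. The comparative figures given.** DSK area: 55 villages, 15,530 households, 76,150 people. GK area: 53 villages, 19,898 households, 99,000 people. The GK area has 28% more households (19,898/15,530). People per village are about 1,385 and 1,868, and people per household 4.90 and 4.98.

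**The case against.** The baseline survey removes constant differences between the areas once changes are compared. This stands, and the table grants it: only variation in change is counted.

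The size rests on an assumed SD, and the inflation vanishes at zero. This also stands. A reader might infer that the intervals are certainly too narrow. The protocol does not show that; it shows only that the design cannot tell. Nor does Data Analysis specify the test calibrated above. It promises intervals, not a p-value.

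A reader might also infer that nothing supports the word 'equivalent'. That is too strong. All four unions lie in one upazila and share one description of curative providers, village counts and household sizes are close, and both NGOs are Plan partners giving primary care. Total population says little about zinc use. What is absent is a stated selection criterion or a baseline comparison on the outcomes.

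Similarly, the Project Summary's phrase about generalisable strategies is an aim, not a stated conclusion. The design is openly labelled controlled before-after.

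A two-against-two permutation argument (smallest one-sided p of 1/6) might seem to settle the matter. No such test is planned, and it treats four unions as exchangeable when NGO and treatment coincide, so the verdict does not rest on it.

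Finally, analysis detail often sits in a statistical analysis plan. But the allocation, the village cluster level, the crude effect measure and the claim are fixed in this protocol, and no later document can add unions.

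**Conclusion.** The point holds as a limit on inference. The arithmetic of 580 is sound for its stated inputs, and more children or villages in the same four unions would not help. The village-clustered intervals are valid for sampling within these unions but leave out differing trends between unions and NGO areas, which cannot be estimated with one NGO area per arm.

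The understatement runs from nil to a true one-sided error of about 17%, for an assumed SD of union-level change of 0 to 5 points. It rests on the plan's variance inputs, independent surveys of 580 per area, and a test of the difference in changes. The study can proceed, but its effect measure and its stated conclusion should change.

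**What to change.** 1. In Data Analysis, replace the crude relative risks as the effect measure with the area-by-time contrast (difference in changes) from the planned village-clustered regression. Adjust it for the child's age, gender and socioeconomic status, which the equity outcome already requires.
2. Report the baseline-to-endline change separately for each of the four unions, as a descriptive consistency check only. It should not become a success rule: if the four unions were exchangeable, both DSK unions would exceed both GK unions by chance 1 time in 6.
3. State that the village-clustered interval is conditional on these four unions and reflects sampling error only. Limit the impact and added-value conclusions in the Project Summary and Rationale to the DSK and GK areas of this upazila.
4. In the Project Summary and Study Design, replace 'equivalent' with 'comparison area', supported by a baseline comparison by area.

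Entering union as a stratum is not a cure for narrow intervals: it treats the four unions as fixed and takes between-union variation out of the standard error.

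**Cost:** a more modest claim, one or two tables and slightly more analysis, with no new data collection. The contrast in item 1 is also less precise than a single endline comparison. With the plan's inputs, 580 per area per survey and no union-level variation, one-sided power for 7.5 points is Φ(0.075/0.0363 − 1.645) = 66%, and this should be disclosed.
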